#### 12.1.2 Randomization and Baseline Visit (V1)

##### 12.1.2.1 Randomization

When all of the inclusion criteria and none of the exclusion criteria are met, the randomization of an eligible patient can take place within the Baseline Visit (see 6).

##### 12.1.2.2 Baseline Visit (V1) - Month 1

Time between Screening Visit and Baseline Visit should not exceed 2 months.

#### The Baseline Visit includes:

- Serum for immune parameters
- FACS and stem cell persistence
- IFNa prediction score
- TKI intake
- AOP2014 dosing and drug accountability (only arm A)
- Physical examination, vital signs and body temperature
- ECOG performance score
- BCR-ABL-PCR test at study reference laboratory in Jena or Mannheim

- Clinical Laboratory Evaluation
- Serum/urine pregnancy test
- Local tolerability assessment (only arm A)
- QoL
- Concomitant medications and AEs

Safety laboratory analysis should not be older than 7 days before start of study treatment with AOP2014 in Arm A. If the Baseline Visit (V1) will not be performed within 1 week from Screening Visit, the safety laboratory analyses assessments have to be repeated on V1 for arm A. This includes: complete blood counts including differential blood count (machine), Na, K, Ca, Krea, Urea, GOT, GPT, AP, GGT, LDH, Bilirubine, total Protein, PT, PTT, Glucose.

At Baseline Visit all of the patient will receive a patient diary. Moreover, patients who were randomized in arm A will be provided with enough pens to last until next scheduled visit.

Female patients are required to have a negative pregnancy test. Additional pregnancy urine tests should be given to woman with childbearing potential in arm A for using at home in case the time between visits exceeds 28 days. The investigator or study nurse has to explain the application of urine pregnancy tests.

### **12.1.3 Visit 2 – 12 (Month 2 – Month 13.5)**

Patients will be seen according to the schedule outlined in study specific procedures for Arm A and B (Table 1 and Table 2). These tables list all necessary assessments and indicate with an “X” when they have to be performed. Each visit can be pre- or postponed by 7 days.

**For patients randomized into arm A,** treatment phase starts with the date of randomization and first AOP2014 injection. Patients randomized into arm A will injected **50 µg AOP2014 at day 0 (Baseline Visit) and 14 days thereafter. From month 2, patients will receive a full dose of 100 µg, every two weeks. First 100 µg dose has to be applied 2 weeks after the last application of 50 µg AOP2014.**

**Importantly, only during the first month AOP2014 will be administered together with the TKI. After one month, the TKI will be stopped.**

**Patients randomized into arm B,** will discontinue TKI one month after randomization. From this moment patient will receive no further treatment.

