| Physical examination / vital
signs / body temperature                                                                          | X                                 | X                   | X                                                                   | X | X | X | X | X | X | X | X   | X  | X  | X  | X                         |                    | X  |    |    | X  |      | X  | X  |            |   |                                      |
| ECOG PS                                                                                                                           | X                                 | X                   | X                                                                   | X | X | X | X | X | X | X | X   | X  | X  | X  | X                         | X                  |    | X  |    |    | X    |    | X  | X          |   |                                      |
| Safety laboratory analyses                                                                                            | X                                 | X                   | X                                                                   | X | X | X | X | X | X | X | X   | X  | X  | X  | X                         | X                  |    |    |    |    |      |    |    |            |   |                                      |
| Blood Count                                                                                                                       |                                   |                     |                                                                     |   |   |   |   |   |   |   |     |    |    |    |                           | X                  | X  | X  | X  | X  | X    | X  | X  |            |   |                                      |
| BCR-ABL transcripts (IS)                                                                                              | X                                 | X                   | X                                                                   | X | X | X | X | X | X | X | X   | X  | X  | X  | X                         | X                  | X  | X  | X  | X  | X    | X  | X  | X          | X |                                      |

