| TKI intake for 30 days                                                                                                            |                                   | X                   |                                                                     |   |   |   |   |   |   |   |     |    |    |    |                           |                    |    |    |    |    |      |    |    |            |   |                                      |
| AOP2014 dosing (biweekly, 50
µg for the first 4 weeks , from
month 2 full dose of 100 µg )
and accounting |                                   | 50 µg        | 100 µg                                                       |   |   |   |   |   |   |   |     |    |    |    |                           |                    |    |    |    |    |      |    |    |            |   |                                      |
|                                                                                                                                   |                                   | X                   | X                                                                   | X | X | X | X | X | X | X | X   | X  | X  | X  |                           |                    |    |    |    |    |      |    |    |            |   |                                      |
| Local tolerability assessment                                                                                                     |                                   | X                   | X                                                                   | X | X | X | X | X | X | X | X   | X  | X  | X  |                           |                    |    |    |    |    |      |    |    |            |   |                                      |
| Quality of life                                                                                                                   |                                   | X                   | X                                                                   | X | X | X | X | X | X | X | X   | X  | X  | X  |                           |                    |    |    |    |    |      |    |    |            |   |                                      |

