**Legend to table 1a and table 1b**

1. Visits can be pre- or postponed by 7 days.
2. Randomization could be done up to two working days prior to potential study treatment start. If the patient will not meet all the inclusion criteria / fulfill the exclusion criteria, or will withdraw his informed consent before the randomization, he/she must be registered by KKS Marburg using the Screening/Randomization form
3. A pre-mature end of treatment (EOT) assessment must be performed before months 15 for reasons outlined in section 13 and latest at the scheduled next visit. A regular end of treatment visit can be pre- or postponed by 10 days.  
**IMPORTANT:** a premature end of treatment, in case of molecular relapse (loss of MMR) or withdrawal of informed consent, irrespective of whether occurring in arms A or B requires to immediately resume TKI therapy. **After the premature EOT Visit has been performed, a molecular BCR-ABL follow up every three months until month 25 is required.** After month 25 off study follow ups will occur annually, as indicated in the flow chart.
4. Safety laboratory analysis should not be older than 7 days before start of study treatment with AOP2014 in arm A. If the Baseline Visit (V1) will not be performed within 1 week from Screening Visit, the safety laboratory analyses assessments have to be repeated on V1 for arm A. This includes: complete blood counts including differential blood count (machine), Na, K, Ca, Krea, Urea, GOT, GPT, AP, GGT, LDH, Bilirubine, total Protein, PT, PTT, Glucose (see 12.1.2 and 12.2.8).
5. BCR-ABL PCR must be performed at one of the two EUTOS-certified laboratories named in section 12.2.10: 20 – 30 ml blood are required.  
BCR-ABL PCR must have been confirmed three times with at least MR^4 please refer to inclusion criterium number 5.
6. For every visit HCG from serum only in Arm A in women of childbearing potential.  
Additional HCG urine test for home use > 28 days only in Arm A in women of childbearing potential.
7. For immune / stem cell marker 30ml (CD86+pDCs) of heparin and 5ml Serum are required (see 12.2.11). Shipment of samples to Marburg should be performed Monday-Thursday and is possible by regular mail.
8. For interferon alpha (IFN) response and adverse event prediction scores (see 12.2.11), please send 9 to 10 ml EDTA peripheral blood (PB) by regular mail to Aachen.

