### 10.3 Selection of dose in the study

In the phase III PROUD-PV study (EUDRA-CT 2012-005259-18), AOP2014 is used at the starting dose of 100µg biweekly. This is equivalent to a pegIFN 2a dose of approximately 70 µg weekly. Previous clinical studies suggested that a dose of 45-90µg pegIFN weekly is therapeutically effective. At the lower dose of 45µg pegIFN weekly was associated with a well manageable toxicity. **Therefore, a dose of 100µg AOP2014 to be administered biweekly was chosen as the standard dose for the ENDURE-CML study.**

To achieve a good tolerability of AOP2014 the study treatment will be escalated to full maintenance dose of 100µg as follows: 50 µg AOP2014 every 14 days for the first 4 weeks. From week 5 patients will receive full dose of 100µg once per two weeks.

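### Arm A's first 100 µg dose is fixed on day 28, but the visit with the first on-treatment safety labs may be up to 7 days later, so the dose can be doubled unchecked

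*Protocol*

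**What the plan says.** **Dose date.** The Synopsis and section 12.1.3 give 50 µg at baseline (day 0) and 14 days later. The first 100 µg "dose has to be applied 2 weeks after the last application of" 50 µg. Section 10.3 agrees: "From week 5 patients will receive full dose of" 100 µg.

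**Labs.** The arm A row "Safety laboratory analyses" in Table 1 is marked at Screening, at Baseline and then from Visit 2 (month 1 after randomization). There is no column between Baseline and Visit 2.

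**Visit window.** Legend note 1: "Visits can be pre- or postponed by 7 days". Section 12.1.3 repeats this.

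**Link between step-up and visit.** The dosing row of Table 1 gives 50 µg for four weeks and then, from "month 2 full dose of 100" µg, with 100 µg starting in the Visit 2 column.

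**Supply.** At baseline, arm A patients "will be provided with enough pens to last until next scheduled visit" (section 12.1.2.2). The Synopsis and section 10.5 allow two injections per pen.

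**Standard at treatment start.** Section 12.1.2.2: "Safety laboratory analysis should not be older than 7 days before start of study treatment with AOP2014".

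**The concern.** Two clocks govern the same step. The dose runs on a fixed 14-day rhythm from the first injection. The visit with the first on-treatment labs runs on months from randomization with a tolerance of 7 days either way. Nothing in the protocol says which gives way when the visit falls after day 28.

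The lab-driven dose reductions for neutropenia, thrombocytopenia and raised transaminases (Tables 3 and 5) can act only on a value that has been measured. Section 10.2 lists leukopenia and thrombocytopenia as very common with AOP2014. On day 28 a patient who follows the Table 1 entry "TKI intake for 30 days" is also still on the TKI. Later injections between visits repeat a dose level that has been checked, whereas this one doubles the dose before the first check. What is at stake is a short, avoidable blind spot in safety monitoring.

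**Working it through.** The protocol states no figure for this gap, so there is none to reproduce. The check is calendar arithmetic.

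**1. Dose date.** 0 + 14 + 14 = day 28. Week 5 also starts on day 28, counting the first injection as day 0.

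**2. Visit 2 window, in days from the first injection.** Let *m* be the length of month 1 and *r* the number of days by which randomization precedes the first injection. The window runs from *m* − *r* − 7 to *m* − *r* + 7. The gap from the 100 µg dose to the labs is *m* − *r* − 28 on schedule and *m* − *r* + 7 − 28 at most.

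The protocol does not give *m* in days. Four weeks fits the AOP2014 dosing row of Table 1, and 30 days is borrowed from the TKI row. Legend note 2 allows randomization up to two working days before treatment start; I assume that this is 2 to 4 calendar days.

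| *m* | *r* | Visit 2 window | Gap on schedule | Largest gap |
|---|---|---|---|---|
| 28 | 0 | 21 to 35 | 0 | 7 |
| 28 | 2 | 19 to 33 | −2 | 5 |
| 28 | 4 | 17 to 31 | −4 | 3 |
| 30 | 0 | 23 to 37 | 2 | 9 |
| 30 | 2 | 21 to 35 | 0 | 7 |
| 30 | 4 | 19 to 33 | −2 | 5 |

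A negative gap means that the labs come first. A 31-day month with *r* = 0 would add one more day (31 + 7 − 28 = 10).

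**3. Age of the latest scheduled lab at the step-up, if Visit 2 is after day 28.** The baseline lab is drawn between 7 days before the first injection and day 0, so its age on day 28 is 28 − 0 = 28 to 28 + 7 = 35 days. At the first 50 µg dose the limit is 7 days.

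**4. Can the dose be taken at home before the visit?** If Visit 2 is planned after day 28, three injections (days 0, 14, 28) precede it. At two injections per pen, 3 / 2 = 1.5, so the dispensing rule calls for two pens. The patient then has the 100 µg dose at home. If only one pen was given and the visit slips, the day-28 dose is late.

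**5. Is a Visit 2 after day 28 foreseen?** Yes. Section 12.2.13 has home pregnancy tests handed out at baseline in case more than 28 days pass before the next visit.

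**6. Which dose rules could a single first on-treatment sample trigger?** Table 3 has four lab-based rows and Table 5 has two. The row for ALT of at least 10 × ULN requires persistence, which one sample cannot show. That leaves at most 6 − 1 = 5 rows.

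**The case against.** The strongest reply is that the protocol does place the step-up at Visit 2. Section 12.1.3 is headed as covering Visit 2 from month 2 and sets the full dose from month 2. Its list of visit procedures includes AOP2014 dosing, and Table 1 puts 100 µg in the same column as the labs. With Visit 2 at four weeks, one pen lasts until the visit and the next is dispensed there. An unchecked step-up then requires a late visit and a second pen handed out in advance. This stands as evidence of intent, and it makes 0 days on schedule and 7 days at most the better reading. It does not close the gap, because the only wording that fixes a day fixes the dose, and no text makes the dose wait for the visit or for a result.

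A second reply is that the lead-in serves tolerability and was never meant as a lab-gated escalation. Section 10.3 says so and gives 100 µg as the starting dose in the phase III polycythemia vera study. Section 10.3.1.1 reports no dose-limiting toxicity up to 540 µg, and entry requires platelets of at least 100 × 10⁹/L and AST and ALT of at most 2 × ULN. This stands too, and it is why the gain is small.

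A reader might infer more, but the documents do not support it:
- That the protocol tells sites to escalate despite known toxicity. Section 10.3.1.1 calls for dose modification when side effects occur, and that covers the step-up.
- That the step-up is unrelated to Visit 2. Table 1 and section 12.1.3 show the opposite intent.
- That the primary endpoint is affected. Nothing here touches relapse assessment at 7 months.

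**Conclusion.** The point holds as a minor gap in the schedule. Following the protocol to the letter, a patient in arm A can go from 50 to 100 µg before any on-treatment blood count or transaminase. The labs then follow at most 7 days later if month 1 is four weeks and 9 days later if it is 30 days. If randomization precedes the first injection by 2 to 4 days, these maxima fall to 3 to 5 and 5 to 7 days.

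The conclusion rests on the planned injection days being kept and on the site dispensing for the interval actually scheduled. Unscheduled labs remain possible, but the protocol does not require them. The documents do not say how many patients would have Visit 2 after day 28, or how many would meet a lab criterion in the first month, so neither is estimated. This is a cheap improvement and does not mean that the dosing scheme is unsafe.

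**What to change.** Add to legend note 1 and to section 12.1.3:

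> In arm A, Visit 2 (including safety labs) takes place on days 21 to 28 after the first injection, and the blood count and transaminases are reviewed before the first 100 µg dose.

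The pen can be dispensed at Visit 2 and the dose confirmed by phone once the results are read, so no pen is withheld and no extra trip is needed. The day-28 dose date stays. Routine postponement to day 35 is not advised: it would leave 35 − 14 = 21 days between injections and, with the TKI stopped on day 30, 35 − 30 = 5 days without TKI before the next interferon dose. That would work against the overlap rationale in section 8.2.2.

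**Cost.** One sentence in two places, a narrower Visit 2 window in arm A, and a result review and phone call by the site. With a four-week month the new window lies inside the present one. With a 30-day month and *r* = 0, days 21 and 22 lie just outside it, so the new sentence should take precedence. Arm B keeps its window, so the Visit 2 PCR and quality-of-life assessments may fall a few days earlier in arm A. Section 12.2.8 sends safety labs to central laboratories without stating a turnaround, so sites should aim for the earlier part of the window.

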**The following tests/evaluations have to be performed:**

- Physical examination, vital signs and body temperature
- ECOG performance score
- BCR-ABL-PCR test at study reference laboratory in Jena or Mannheim
- Clinical Laboratory Evaluation
- Serum/urine pregnancy test
- Autoimmunity screen (only arm A: Visit 2 and Visit 8)
- Serum for immune parameters (only Visit 8)
- FACS and stem cell persistence (only Visit 2 and Visit 8)
- IFNa prediction score (only Visit 2, Visit 8 and Visit 11)
- AOP2014 dosing and drug accountability (only arm A)
- Local tolerability assessment (only arm A)
- QoL
- Concomitant treatments and AEs

Additionally, at each visit, patients (arm A) will be provided with enough pens to last until next scheduled visit.

#### **12.1.4 End-of-Treatment assessment Visit 13 (Month 15)**

A regular End-of-Treatment (EOT) assessment will be performed 15 months after randomization in **arms A and B** (procedures are outlined in Table 1 and Table 2).

Patients who relapse or otherwise discontinue the study treatment prematurely, before month 25, will also undergo an EOT visit prematurely; see 12.1.5. This visit should be scheduled closely to the date when the reason leading to treatment discontinuation (see 13) occurred, but latest at the date of the scheduled next visit. The further molecular BCR-ABL RT-PCR (IS) follow up will then be every three months until month 25 (12.1.6). A molecular and demographic/clinical Post Study Follow Up will be once every year for another 3 years (see study flow chart 1.1, Table 1 and Table 2 and 12.1.7).

**IMPORTANTLY:** In case of molecular relapse (loss of MMR) or withdrawal of informed consent TKI treatment must be resumed immediately in **arms A or B**, irrespective of the phase of study.

#### **12.1.5 Premature End-of-Treatment assessments**

Patients, who relapse **in arm A or arm B**, will resume TKI therapy and perform an early (premature) EOT visit. The molecular BCR-ABL RT-PCR (IS) follow up will then be performed and documented in the e-CRF (every 3 months after resuming the TKI as in surveillance phase until month 25 (see study flow chart 1.1 and Table 1 and Table 2).

#### **12.1.6 Surveillance phase (month 15 to month 25)**

In **arm A** surveillance phase refers to the time between month +15 to +25 (see study flow chart 1.1 and Table 1 and Table 2).

CAVE: the scheduled follow up differs slightly in arm A compared to arm B in that additional BCR-ABL RT-PCR (IS) assessments are required 16, 17, 19, 20, and 22.5 months after randomization (see study flow chart 1.1 and Table 1 and Table 2).

For patients randomized into **arm B**, surveillance phase refers to the entire time between month 0 to 25, because these patients never receive any study specific medication.

Patients, who relapse during surveillance phase **in arm A or arm B**, will resume TKI therapy and again perform an EOT visit; see 12.1.5. The molecular BCR-ABL RT-PCR (IS) follow up will then be performed and documented in the e-CRF (every 3 months after resuming the TKI until month 25 (see study flow chart 1.1 and Table 1 and Table 2).

#### **12.1.7 Post Study Follow Up (PSFU)**

Patients, who are in TFR 25 months after randomization, are recommended to undergo quantitative BCR-ABL RT-PCR (IS) monitoring every three months. However, an “off study” documentation of molecular remission will be required only once yearly for three years, namely 36, 48 and 60 months after randomization (see study flow chart 1.1 and Table 1 and Table 2). For all patients, the following data will be documented in PFSU 36, 48 and 60 months after randomization:

- a) Survival (y/n)
- b) Type of current treatment for CML
- c) Demographic data including treatment history and relevant medical history (secondary malignancies, cardiac disease, auto-immune disease, progression of CML)
- d) BCR-ABL RT-PCR (IS)

### 12.1.8 Study Schedule

- Recruitment period (months): 18  
Duration of study per patient (months): 25
- First patient in to last patient out (months): 43
- End of the study (months): after 49

**End of the study is defined as “Last Patient Last Visit and Database Closure”.**

- Post Study Follow Up (months): 35

## 12.2 Study methods

### 12.2.1 Demography

Examined demographics include for example age and sex (see also 16.3).

### 12.2.2 EUTOS Score

The European Treatment and Outcome Study (EUTOS) risk score for chronic myeloid leukemia (CML) was derived from multivariate analysis of response of 2060 patients treated with imatinib for CML between 2002 and 2006. The score is applied at diagnosis, before starting therapy. The EUTOS score is calculated as (7 x basophil) + (4 x spleen), where “basophil” is basophils as a percentage of peripheral blood leukocytes and “spleen” is spleen size palpable below left costal margin .

**The EUTOS score can be calculated online at: <http://bloodref.com/myeloid/cml/eutos>.**

### 12.2.3 Euro and Sokal Scores

The Euro and Sokal scores  are calculated based on the following clinical and laboratory parameters that have to be assessed prior to CML –specific therapies including other than TKI. The Euro and Sokal scores can be calculated online at: <http://bloodref.com/myeloid/cml/sokal-hasford>. More information on the calculation of EUTOS, Euro, and Sokal score is available under: .

